### Recruitment {15}

Paid print advertising will be used to promote the study to individuals in the community who fit the age requirement and meet study inclusion criteria. Recruitment will also be open to people who hear about the study from friends, relatives, or other sources.

## Assignment of interventions: allocation

### Sequence generation {16a}

Participants will be randomized on study entry to one of three treatment groups in a 1:1:1 ratio using computer-generated blocks; blocks of 9 participants will be used to ensure equal group numbers throughout the recruitment and enrolment period. Study participants will be allocated a Revitive device (identified by a model number which distinguishes Revitive Medic^©^ Program 1, Revitive^®^ Program 2, and Revitive sham) according to the randomization schedule.

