### Trial design {8}

This is a single-center, single (participant)-blind, parallel-group, randomized, placebo-controlled (sham group), interventional study. Participants will be randomized to 1 of 3 groups (1:1:1) with each study group receiving a different type of NMES:Group 1—Revitive shamGroup 2—NMES using Revitive Medic^©^ Program 1Group 3—NMES using Revitive^®^ Program 2.

Each participant will be instructed to self-administer the foot NMES device for 30 min twice daily over 8 weeks. Treatment will be administered in a seated position with the participant placing the soles of their feet onto the rubberized foot plates. The device is timed to run continuously for 30 min.

A hierarchical testing approach will be used with comparison of Revitive sham versus Revitive Medic^©^ Program 1 as the primary endpoint; if a statistically significant difference is seen for the primary endpoint, Revitive sham versus Revitive^®^ Program 2 will be tested as a secondary endpoint. The study will investigate if Revitive Medic Program 1 is “superior” compared to Sham, and if that is true, then will go on to investigate if Revitive Program 2 is ‘superior’ compared to Sham.

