### Eligibility criteria {10}

Eligible participants will be community-dwelling adults aged > 65 years who have one or more of the following symptoms in one or both legs: aching/pain in the leg, heaviness in the leg, tiredness in the leg, or cramps in the leg at any time in the day or night.

Exclusion criteria will comprise (but not limited to) severe diabetes mellitus with severe diabetic neuropathy; lumbar radiculopathy; restless legs syndrome; active cancer; standard contraindications to NMES treatment such as the presence of an electronic implanted device (e.g., cardiac pacemaker); any significant injury to the leg(s) in the last 6 months; being non-ambulant; inability to communicate in English; and inability to provide informed consent.

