**Fig. 1 Fig1:**
[figure not shown]
Design of the NMES stimulation trial

Potential participants who express an interest in the study will be contacted by telephone and provided with further information about the study, any questions will be answered and initial screening assessments conducted to inform on eligibility. Once an interested participant is deemed suitable for the study, they will be sent the participant information sheet, randomized, and an appointment will be made to attend the baseline visit; the baseline visit will be arranged for after the participant has had sufficient time to consider the participant information sheet (at least 2 days). Potential participants will be provided with an opportunity to ask questions and request further information about the study at the baseline visit; the participant will also have eligibility criteria checked and provide informed consent. Subsequent procedures will only be initiated once the participant has provided written informed consent.

The participant will undergo baseline assessments and be allocated their study device. Participants will then be instructed as to the correct use of their device and undergo a Doppler assessment of deep leg blood flow volume and intensity both before and during device use. Participants will be sent home with their device to use over the 8-week treatment period.

Participants will return to the study center after 8 weeks (at the end of the treatment period) for study assessments and to return their study device; they will remain on-study for another 4 weeks (follow-up period) during which time they will not use the device. Participants will return to the study center for week 12 assessments, after which they will be considered as having completed the study.

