### Concealment mechanism {16b}

At the time of recruitment, the researcher will allocate participant numbers sequentially to all participants. Each participant number has a pre-allocated study group as per the concealed randomization table, which the researcher is unaware of at the time of recruitment thus avoiding selection bias. Participants will be blinded to their intervention allocation throughout the trial and informed that they have a one in three chance of being randomized to a particular treatment group. It will not be possible to differentiate active and sham devices, as the packaging and appearance of all devices are identical. The same detailed “Instructions for Use” are given to participants regardless of the device they receive. Description of the sensations that can be experienced while using the device will be the same for all participants (a range of sensations from light tingling and feelings of pins and needles to noticeable muscle twitch and contractions in the feet and legs).

Familiarization and ongoing support with the device will be managed by the investigator, who will provide feedback and cues to the participant that their sensations/feelings in response to using the device are as expected/normal.

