## Assignment of interventions: blinding

### Who will be blinded {17a}

This will be a single-blind study with trial participants blinded as to the assignment to their study intervention. Conducting a double-blind study is not feasible, as the therapeutic functioning of the NMES device is dependent on reaching an intensity that results in visible contraction of the calf muscle; as such, the study assessor would be aware of whether the participant used an active or sham device during blood flow measurement.

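### One fixed block size of 9, with an unblinded investigator, makes allocation partly predictable, so the claim that selection bias is avoided is not supported

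*Protocol article*

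**What the plan says.** Protocol article, Trial design {8}: "This is a single-center, single (participant)-blind, parallel-group, randomized, placebo-controlled (sham group), interventional study". No stratification is mentioned.

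Sequence generation {16a}: "Participants will be randomized on study entry to one of three treatment groups in a 1:1:1 ratio using computer-generated blocks", and "blocks of 9 participants will be used to ensure equal group numbers throughout the recruitment and enrolment period". No variation or withholding of the block size is described. The allocated device is "identified by a model number which distinguishes Revitive Medic^©^ Program 1, Revitive^®^ Program 2, and Revitive sham".

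Concealment mechanism {16b}: participant numbers are given sequentially at recruitment. Each number has a pre-assigned group in a concealed table, "which the researcher is unaware of at the time of recruitment thus avoiding selection bias". The investigator runs device familiarization.

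Implementation {16c} has the investigator generate the sequence, enrol participants and assign them. Who will be blinded {17a} says that only participants are blinded and that "the study assessor would be aware of whether the participant used an active or sham device during blood flow measurement".

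The consent section {26a} places randomization after the telephone call. Participant timeline {13} places device issue at the later baseline visit, where "the participant will also have eligibility criteria checked and provide informed consent".

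**The concern.** Hiding the table protects the next assignment only if that assignment cannot be inferred in some other way. Here every block holds three places per arm, the person who issues devices sees which arms have been used, and number order is block order. Anyone who also knows that the size is 9 can count off what remains.

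The inference could be acted on at two points: at the telephone call, where the decision to enter someone is made and the number given, and at the baseline visit, where eligibility is checked again. The ITT population is restricted to eligible participants who used their device at least once, so a person turned away at baseline leaves the primary analysis. At stake is the comparability of the Program 1 and sham groups on a self-rated, interview-based outcome (COPM-P), recorded on a form that the unblinded investigator administers.

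**Working it through.** **Inputs.** Block size 9, ratio 1:1:1, so 3 per arm per block ({16a}); N = 117, 39 per arm (Sample size {14}); one centre ({8}). One unstratified sequence is assumed because no strata are stated. The guesser is assumed to know the block size.

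**The plan's own figure.** 117 / 9 = 13 complete blocks, and 13 × 3 = 39 per arm. This agrees with the stated sample size.

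**Upper bound: every earlier device in the block has been seen.**

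- *Exact arm certain.* This holds along the run of identical arms that ends the block. Expected run length = 1 + 2/8 + (2/8)(1/7) = 9/7. Per assignment, (9/7)/9 = 14.3%; over 13 blocks, 13 × 9/7 = 16.7 of 117.
- *Sham or active certain.* Expected active assignments after the last sham = 6/4; expected shams after the last active = 3/7. The sum is 27/14 per block, (27/14)/9 = 21.4%, or 25.1 of 117.
- *Best guess.* Always naming an arm with the most places left is right for 4.787 of 9 assignments (exact enumeration): 53.2%, against 33.3% by chance.

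**With earlier devices unseen.** Numbers are given at the telephone stage and devices issued later, so the most recent participants' arms may not yet be visible. With L of them unseen, certainty requires a final run longer than L.

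- *Exact arm.* L = 1: 9/7 − 1 = 2/7. L = 2: (2/8)(1/7) = 1/28. L = 3: 0.
- *Sham status.* L = 1: 27/14 − 1 = 13/14. L = 2: subtract the chance that the last two agree on sham status, (6×5 + 3×2)/(9×8) = 1/2, giving 3/7. L = 3: subtract (6×5×4 + 3×2×1)/(9×8×7) = 1/4, giving 5/28.

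Dividing each by 9:

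| Earlier devices unseen | Exact arm certain | Sham status certain | Best guess right |
|---|---|---|---|
| 0 | 14.3% | 21.4% | 53% |
| 1 | 3.2% | 10% | 46% |
| 2 | 0.4% | 5% | 43% |
| 3 | 0% | 2% | 40% |

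The article does not state how many were waiting. An average of 117 over three years is about 0.75 per week, but Trial status reports a COVID-19 delay followed by much faster recruitment, so the queue was probably longer in the later phase.

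**Randomly varying sizes (6, 9, 12).** For a guesser who knows the set of sizes and has seen all earlier devices, simulation gives about 2% certain, about 4% sham status certain and a best guess right 52% to 53% of the time. Varying the size removes most certain predictions and lowers the guess rate little.

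**The case against.** The strongest reply is that this problem depends on Implementation {16c}. Counting off a block requires knowing its size, and {16c} is the main ground for thinking that the enrolling person knew it. Read literally, {16c} means that this person holds the list and all 117 assignments are knowable, so counting adds nothing. If a third party generated the list, the size could be withheld with it. Publication of the size is no evidence of disclosure during recruitment, because the article was submitted after recruitment closed. This largely stands. A reader might infer that the flaw survives third-party generation whatever else is done; it survives only if enrolling staff are still told the size. The two repairs therefore belong together.

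Second, a reader might take 14% to 21% as the share of assignments actually foreseen. The documents do not support that. Those figures need every earlier device to be seen and attendance in number order, neither of which is stated. At the telephone stage the lower rows of the table are more realistic.

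Third, the wording "Exclusion criteria will comprise (but not limited to" might be read as open-ended discretion to exclude. In a condensed article it more likely abbreviates a longer list, so no weight is placed on it.

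Fourth, a block of three times the number of arms is a common choice and not an error in itself. That is accepted. Identical packaging, which {16b} also relies on, protects participants but not staff who allocate by model number.

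**Conclusion.** The concern holds in a limited form. With one fixed block size, sequential numbering, one centre and an unblinded investigator who issues arm-identifiable devices and is said to generate the sequence, allocation is partly predictable. An unseen table alone does not justify saying that selection bias is avoided.

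The upper bound is about 17 of 117 assignments certain and 53% correct guesses. With one to three devices unseen, certainty is 3.2% to 0%, while correct guesses remain at 46% to 40%, still above 33%. All these figures assume that the guesser knows the block size.

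A reader might go on to infer that selection took place or that the Program 1 effect is biased. Nothing in the article shows this; the finding is that the stated reassurance is unsupported. The fault is worth correcting, but {16c} is the more serious weakness in concealment.

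**What to change.** **Design text ({16a} and {16c}).** Have the sequence generated by someone not involved in enrolment or device issue, with block sizes varying at random (for example 6, 9 and 12) and withheld from enrolling staff. The varying size is a setting in the randomization program. The downside is a small possible imbalance if recruitment stops mid-block.

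**This trial.** Trial status reports recruitment complete on 30 June 2022, so the sequence cannot be changed. Instead:

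1. In {16b}, delete the clause claiming that selection bias is avoided, and state that allocation was partly predictable to unblinded staff.
2. Add one sensitivity analysis (Berger-Exner). Refit the primary COPM-P ANCOVA with, as an added covariate, each participant's probability of Program 1 given the earlier allocations in the block: (3 − a)/(9 − k), where k is the number already allocated in the block and a the number of those on Program 1. Report whether the Program 1 effect changes, and compare baseline COPM-P and age by that probability.
3. State that this check detects only selection from guessing on past allocations. It does not detect selection by someone who knew the list, so a reassuring result does not dispose of the problem in {16c}.

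The cost is one deleted clause, one added sentence, and one extra model with two baseline comparisons from data already held.

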### Concealment mechanism {16b}

At the time of recruitment, the researcher will allocate participant numbers sequentially to all participants. Each participant number has a pre-allocated study group as per the concealed randomization table, which the researcher is unaware of at the time of recruitment thus avoiding selection bias. Participants will be blinded to their intervention allocation throughout the trial and informed that they have a one in three chance of being randomized to a particular treatment group. It will not be possible to differentiate active and sham devices, as the packaging and appearance of all devices are identical. The same detailed “Instructions for Use” are given to participants regardless of the device they receive. Description of the sensations that can be experienced while using the device will be the same for all participants (a range of sensations from light tingling and feelings of pins and needles to noticeable muscle twitch and contractions in the feet and legs).

Familiarization and ongoing support with the device will be managed by the investigator, who will provide feedback and cues to the participant that their sensations/feelings in response to using the device are as expected/normal.

### Implementation {16c}

The investigator will generate the allocation sequence and enroll and assign participants to interventions.

## Assignment of interventions: blinding

### Who will be blinded {17a}

This will be a single-blind study with trial participants blinded as to the assignment to their study intervention. Conducting a double-blind study is not feasible, as the therapeutic functioning of the NMES device is dependent on reaching an intensity that results in visible contraction of the calf muscle; as such, the study assessor would be aware of whether the participant used an active or sham device during blood flow measurement.

### Procedure for unblinding if needed {17b}

N/A—this is a single-blind trial with only the participant being unaware of their allocated treatment group, therefore unblinding is not necessary.

## Data collection and management

### Plans for assessment and collection of outcomes {18a}

Outcome and baseline trial data will be collected using a case report form administered by the investigator at each study visit. Images and data from the Doppler ultrasound will be acquired electronically at the baseline visit.

#### Compliance

At the baseline visit, participants will be asked to keep a daily record of treatment sessions undertaken. In the rare event that one or more sessions are missed, participants will be required to keep a written record of those events and report them to the investigator at the week 8 visit. The investigator will document the total number of sessions missed by each participant during the intervention period. Data from participants who miss interventions will be analyzed.

#### Canadian occupational performance measure

The COPM [30] was developed to identify and prioritize participant-specific occupational problems and evaluate changes in these areas using a semi-structured interview; the individual is encouraged to identify activities that he or she wants, needs, or is expected to do but cannot, or those in which the individual is not satisfied with their current performance. The COPM is a generic measure meaning it can be used in all populations, as long as participants are able to reflect on their lives and activities and communicate on these aspects.

The COPM has been assessed as a validated tool that provides novel information when used to assess change in score over time for an individual participant [31–33].

COPM is considered a valid, reliable, clinically useful, and responsive outcome measure and has been widely used to assess change in interventional studies in community populations including the elderly [28, 34, 35].

#### Pain and symptom scores

Pain and symptom scores will be assessed at weeks 0, 8, and 12 with participants asked to indicate pain and symptoms (heaviness, tiredness, aching, cramps) they experience and rank them on a 0 to 10 numerical rating scale.

#### Deep leg blood flow volume and flow intensity

Deep leg blood volume will be assessed using Doppler ultrasound before and during the use of the Revitive device [36]; the IsoRocker on the Revitive device will be disabled during Doppler ultrasound, to minimize movement during assessment. Blood flow will be measured at the medial aspect of the ankle between the medial malleolus and the Achilles tendon, using the appropriate arterial ultrasound probe and pre-set volume flow algorithms on a duplex ultrasound machine. Two sets of recordings will be taken, pre-stimulation and 30 s into Waveform 5. Five seconds worth of data will be recorded at each time. The recording will then be broken down into individual frames, saved onto the scanner, and analyzed mathematically by MATLAB [36]. MATLAB analysis of frames determines peak flow volume and the peak intensity of flow within those 5 s. If baseline visit data are of insufficient quality due to noise, Doppler ultrasound can be repeated at week 8.

### Plans to promote participant retention and complete follow-up {18b}

Participants will be advised at their baseline assessment visit that telephone/email/text/social media support is available and they will be encouraged to contact the trial investigator to discuss any questions or difficulties they have.

Participants who discontinue the trial early will be asked if they agree to completing follow-up and having their data included in the final analysis.

### Data management {19}

Study data will be transferred, by the investigator, from the paper case report form into an electronic database on completion of subject participation. Hard-copy data will be stored in secure locked storage at the study site; electronic data will be stored at the study site using sponsor data security systems. Significant data errors (range checks) will be monitored for during data analysis. Data analyses will be conducted and reported in accordance with Consolidated Standards Of Reporting Trial guidelines for non-drug trials.

### Confidentiality {27}

All data will be handled in accordance with the UK Data Protection Act 2018. Case report forms do not bear the participant’s name or other identifiable personal data. Participants will be sequentially assigned a trial identification number upon enrolment into the study, and the study site will maintain a master participant identification log.

All individual participant information will be de-identified during the reporting of data and resulting publications or presentations, to fully protect participant confidentiality. Participants will be informed that information or reports from the study will be prepared and submitted for publication. Participant information will normally be presented as group data. If necessary, information obtained from specific individuals may be presented but names will not be used. Participants will only be identified in such publications by their identification number and possibly their age and gender.

### Plans for collection, laboratory evaluation, and storage of biological specimens for genetic or molecular analysis in this trial/future use {33}

N/A—no biological specimens will be collected.

## Statistical methods

### Statistical methods for primary and secondary outcomes {20a}

Analysis of covariance (ANCOVA) will be used to compare Revitive Medic^©^ Program 1 versus Revitive sham and Revitive^®^ Program 2 versus Revitive sham at weeks 8 and 12, with change from baseline as the dependent variable, and treatment group and baseline value as independent variables. Least square means for each group, treatment differences, 95% confidence intervals (CIs) and *p*-values will be calculated. Model assumptions will be checked and, if departures from normality are evident, a Wilcoxon rank sum test and associated 95% CI using the Hodges Lehmann estimator will be used to compare groups.

Logistic regression with baseline value as a covariate and treatment group as a classification variable will be used to compare the proportion of responders in each test group versus the sham group. Treatment effect will be estimated as an odds ratio (test/sham), with 95% CIs and associated *p*-value. An odds ratio of > 1 indicates a better outcome in the test group.

For all parameters at each time-point, only participants with both a baseline and the corresponding post-treatment assessment will be included in the calculation of change from baseline.

Any subgroup analysis based on factors such as, for example, age or co-morbidities in a study of this size (< 40 per group) is going to have limited power to show differences within these subgroups. Therefore, any such analysis will be of limited value. However, further exploratory analyses, investigating the effects of other covariates (such as age and BMI), may be undertaken for the study outcomes and provided as supportive information.

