### Outcomes {12}

The primary endpoint for the study comprises a comparison of change in Canadian Occupational Performance Measure Performance (COPM-P) score from baseline to Week 8 for Revitive Medic^©^ Program 1 versus Revitive sham. COPM-P score is a self-evaluation measure of each participant’s current physical/ occupational performance status.

Secondary endpoints comprise:Change in COPM-P from baseline to week 12, comparing Revitive Medic^©^ Program 1 versus Revitive sham.Change in COPM-P from baseline to weeks 8 and 12 comparing Revitive^®^ Program 2 and Revitive sham.Change in Canadian Occupational Performance Measure Satisfaction (COPM-S) score from baseline to week 8, comparing Revitive Medic^©^ Program 1 versus Revitive sham and Revitive^®^ Program 2 versus Revitive sham. COPM-S score is a self-evaluation measure of each participant’s current satisfaction with their relevant physical/occupational performance.Change in leg pain from baseline to weeks 8 and 12, comparing Revitive Medic^©^ Program 1 versus Revitive sham and Revitive^®^ Program 2 versus Revitive sham; participants will rate leg pain using an 11-point numerical rating scale.Change in blood flow volume and intensity from baseline during device use, comparing Revitive versus Revitive sham.Change in symptom score from baseline to weeks 8 and 12 in terms of overall symptom score and each item (heaviness, tiredness, aching, and cramps), comparing Revitive Medic^©^ Program 1 versus Revitive sham and Revitive^®^ Program 2 versus Revitive sham.

Assessments conducted at the different study visits are presented in Table 1.

**Table 1 Tab1:** Study assessments in the NMES stimulation trial

	**Telephone assessment (≥ week − 1)**	**Baseline assessment** **(week 0)**	**Treatment period**	**Week 8**	**Week 12**
Eligibility	x	x			
Randomization	x				
Informed consent		x			
Demographics		x			
Medical history	x	x	x	x	x
Medications	x	x	x	x	x
Device issue and familiarization		x			
Device usage		x	x	x	
COPM		x		x	x
Symptom (heaviness, aching, tiredness, and cramps) scores		x		x	x
Leg pain		x		x	x
Doppler ultrasound		x		x^a^	
Adverse events		x	x	x	x

^a^For participants with poor quality Doppler data at week 0

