### Sample size {14}

The sample size for the study is 117 participants, with 39 participants in each treatment group.

At the time of protocol development, the anticipated effect of Revitive Medic^©^ Program 1, Revitive^®^ Program 2, and Revitive sham on the primary outcome (COPM-P) was not understood. Multiple publications [27–29] have cited an improvement of 2 points in COPM-P score for an individual participant as a minimally clinically important difference (MCID); a 2-point change in COPM was therefore set as the threshold required for a participant to be considered a responder to the study intervention.

An absolute difference of 30% in the proportion of participants that meet the COPM-P responder definition (improvement of 2 points) between Revitive sham and Revitive Medic^©^ Program 1 or Revitive^®^ Program 2 was considered necessary to demonstrate a clinically meaningful difference for either test device. To control Type I error, a single primary endpoint was chosen namely the difference between Revitive sham and Revitive Medic^©^ Program 1; a comparison of Revitive sham and Revitive^®^ Program 2 is a secondary endpoint. A sequential testing procedure will be employed such that the secondary endpoint can only be formally assessed if the primary endpoint achieves statistical significance (*p* < 0.05).

Basing the sample size calculation on this design, it was determined that 39 participants would be needed in each of the three intervention groups to show an absolute difference of 30% in the proportion of responders between Revitive sham and Revitive Medic^©^ Program 1 or Revitive^®^ Program 2 at 80% power and two-sided 5% significance. For the purposes of the power calculation, the comparison used a Pearson chi-square test at the two-sided significance level (*p* < 0.05).

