#### Canadian occupational performance measure performance score

The best possible score for COPM-P is 10 points. Any participant with a score of 10 at baseline will be excluded from the modified intent-to-treat (mITT) population, since the condition of interest is absent in these participants. Gains of at least 2 points in COPM are considered clinically important (MCID; 27–30). Using this threshold, participants will be classified as either a responder (change in COPM-P of ≥ 2) or non-responder (change in COPM-P of < 2) at weeks 8 and 12. The proportion of responders at each time point will be summarized by treatment group. Responder analysis will be performed for the intent-to-treat (ITT), mITT, per protocol (PP) populations, and also the subset of participants with a baseline score of ≤ 8 (since participants with a baseline score of > 8 cannot meet the MCID).

For ANCOVA and logistic regression, a hierarchical testing procedure will be used to maintain the Type I error rate at 5%. Firstly, the statistical significance of Revitive Medic^©^ Program 1 versus Revitive sham will be calculated, and if the *p*-value is ≤ 0.05 testing will proceed to Revitive^®^ Program 2 versus Revitive sham (also at the 5% significance level). If Revitive Medic^©^ Program 1 versus Revitive sham has a *p*-value of > 0.05, then the difference between Revitive^®^ Program 2 and Revitive sham will be considered non-significant but a *p*-value will be presented for descriptive purposes.

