For statistical analysis, multiple imputation will be used to handle missing data. It will be assumed that data are missing at random. If the pattern of missing data is non-monotone, then partial imputation will initially be carried out (just enough to get the monotone missing data pattern) using the Markov Chain Monte Carlo method. Once the data exhibit a monotone missing data pattern, the monotone regression method will be used to impute the remaining missing data. The regression model will include terms for treatment and the observed values at visits prior to the missing value. For each endpoint, 20 imputed datasets will be created and analyzed, and the results will be pooled using the MIANALYZE procedure. Sensitivity analysis will be performed whereby missing data will be replaced by the value recorded at baseline (baseline observation carried forward).

For COPM-P responder analyses, participants who do not have an assessment for a visit will be categorized as responders or non-responders according to the value obtained via the multiple imputation; for sensitivity analysis, they will be classified a non-responder (non-responder imputation) at that visit.

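### A judgement of non-normality can replace the baseline-adjusted primary ANCOVA with an unadjusted Wilcoxon test; the switch is not needed for validity and fits neither the hierarchy nor the pooling as written

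*Protocol article*

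**What the plan says.** All references are to the protocol article.

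- **Endpoint**: the section Outcomes {12} defines it for Program 1 against sham, in these words: "The primary endpoint for the study comprises a comparison of change in Canadian Occupational Performance Measure Performance (COPM-P) score from baseline to Week 8".
- **Main model** (Statistical methods {20a}): ANCOVA "with change from baseline as the dependent variable, and treatment group and baseline value as independent variables", reported as least-squares means, differences, 95% CIs and p-values.
- **Fallback** (same section): after checking model assumptions, "if departures from normality are evident, a Wilcoxon rank sum test and associated 95% CI using the Hodges Lehmann estimator will be used". This is worded as a replacement for the group comparison, not as a supplement to it.
- **Hierarchy** (COPM performance score): "For ANCOVA and logistic regression, a hierarchical testing procedure will be used to maintain the Type I error rate at 5" per cent. Program 2 is tested formally only if Program 1 succeeds. The rank test is not named.
- **Missing data** ({20c}): "For each endpoint, 20 imputed datasets will be created and analyzed, and the results will be pooled using the MIANALYZE procedure".
- **Scale** (COPM performance score): "The best possible score for COPM-P is 10 points". The same section notes that someone starting above 8 cannot gain the 2 points that define response.
- **Blinding** ({17a}, {17b}): only participants are blinded.

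**The concern.** A score with a ceiling of 10 makes some non-normality in the residuals plausible, so the fallback could well come into play. Four things then follow.

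1. The test that yields the primary p-value is settled by a judgement made on study data. That p-value also opens the gate to Program 2, so both confirmatory claims hang on it.
2. The rank-sum test compares two groups and has no covariate. Baseline adjustment disappears on a scale where baseline limits the possible change.
3. The reported quantity moves from a baseline-adjusted mean difference to an unadjusted Hodges-Lehmann shift.
4. Neighbouring sections are written for model output. The hierarchy names only ANCOVA and logistic regression, and MIANALYZE combines estimates with standard errors, whereas a rank-sum p-value is neither.

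**Working it through.** **Step 1. The plan's own figure.** Sample size {14} gives 39 per group for a 30-point difference in responders, "at 80% power and two-sided 5% significance", by Pearson chi-square. The sham rate is not stated; assume 20% against 50%, mean 35%:

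n = [1.96·√(2·0.35·0.65) + 0.8416·√(0.20·0.80 + 0.50·0.50)]² / 0.30² = (1.322 + 0.539)² / 0.09 ≈ 38.5, so 39.

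The figure is reproduced (50% against 80% gives 39 too). It concerns a responder test, so the article contains no power figure for either the ANCOVA or the Wilcoxon test on change.

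**Step 2. Cost of dropping baseline with normal errors.** Let r be the baseline-to-week-8 correlation, with equal SDs. Residual variance is 1 − r² for ANCOVA and 2(1 − r) for raw change, a ratio of (1 + r)/2. The Wilcoxon test has efficiency 0.955 relative to the t-test.

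- r = 0.3: 0.955 × 0.65 = 0.621; 39/0.621 ≈ 63 per arm to match ANCOVA at 39
- r = 0.5: 0.955 × 0.75 = 0.716; about 55 per arm
- r = 0.7: 0.955 × 0.85 = 0.812; 48 per arm

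This is not the cost of the rule itself, because with normal errors the rule seldom switches. Step 3 addresses that.

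**Step 3. The rule as a whole.** Simulation with 39 per arm, two-sided 5%, 4,000 runs per scenario, and an effect giving ANCOVA about 80% power with normal errors. Assumed trigger: Shapiro-Wilk p < 0.05 on the ANCOVA residuals. Assumed r: 0.3/0.5/0.7. Monte Carlo standard error near 80% is √(0.8·0.2/4000) ≈ 0.6 points.

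| Errors | Switch fires (%) | ANCOVA power (%) | Rule with switch (%) | Difference (points) |
|---|---|---|---|---|
| Normal | 5/4/5 | 79.0/78.7/79.4 | 78.0/78.5/79.0 | −1.0/−0.2/−0.4 |
| Moderate skew (gamma, shape 2) | 99/99/99 | 79.0/79.6/79.4 | 64.5/72.8/79.0 | −14.5/−6.8/−0.4 |
| Strong skew (lognormal) | 100/100/100 | 80.2/81.6/81.4 | 74.5/86.2/93.1 | −5.7/+4.6/+11.7 |
| Heavy tails (t, 3 df) | 78/77/77 | 83.2/81.4/82.9 | 75.4/82.6/88.7 | −7.8/+1.2/+5.8 |

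A separate check with a moderate skew for which the trigger fired in about 85% of trials gave Wilcoxon power of 64/69/76%, with ANCOVA at 79–84% across all shapes in that check. There, rank ANCOVA with baseline matched or beat the unadjusted Wilcoxon in nearly every scenario.

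**Step 4. Type I error.** Under the null in the Step 3 scenarios, ANCOVA gave 4.1–5.3% and the mechanical two-stage rule 4.6–5.6%. If the smaller of the two p-values were always taken (normal errors, 10,000 runs), the error rate was 8.0/7.0/7.0%.

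**The case against.** **The fallback need not lose power.** A reader might infer that the rule always weakens the primary test, perhaps from the normal-error comparison in Step 2. The documents do not support that. With normal errors the rule rarely leaves ANCOVA and loses a point at most. Where it does fire, the direction depends on shape and correlation. In another setting (shift of 0.6 SD, lognormal errors, baseline-to-change correlation −0.3/−0.5/−0.6) Wilcoxon power was 99/94/91% against 82/88/90% for ANCOVA. This objection stands: the power effect can only be stated conditionally.

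**Rank results can be pooled.** A reader might also infer that the fallback makes the imputation plan unusable. It does not. Imputation is attached to the endpoint and precedes the test, and a Hodges-Lehmann estimate with the standard error implied by its CI can be combined approximately by Rubin's rules. Nothing says the fallback uses complete cases. What remains is that no pooling is described for this branch.

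**A threshold for non-normality and a pooling recipe belong in the SAP.** True for a condensed article, so their absence is not the point. The point is the stated rule, which lets a data check replace the primary analysis.

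**Error control is not shown to fail.** The text ties the switch to assumption checks, not to significance, so the 7–8% figure describes misuse of the discretion, not expected behaviour.

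**The estimand may not change.** Under a pure location shift both methods target the same shift. They diverge if treatment alters the shape of the distribution, which the ceiling could cause.

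**Conclusion.** The concern holds in a limited form. The article makes the primary test depend on a look at the data, and the alternative drops baseline, may answer a different question, and does not connect with the hierarchy or the pooling as written.

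The size is conditional on assumed error shapes, correlations and trigger. Under moderate skew the loss ranges from about 15 points of power at r = 0.3 to a few points or none at r = 0.7. Under strong skew or heavy tails it is about 6 to 8 points at r = 0.3, turning into gains of about 1 to 12 points at r = 0.5 and 0.7. Type I error is near nominal with a mechanical trigger.

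The decisive result is that ANCOVA held its size and about 80% power in every shape tried at 39 per arm, so validity does not require the switch. The conclusion is neither that the trial is underpowered by this rule nor that its error rate is inflated as planned. It is that an avoidable data-dependent choice sits in the primary analysis and can be removed almost for free.

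**What to change.** State in {20a} that ANCOVA with baseline as covariate is the only primary analysis of COPM-P change at week 8, whatever the residual checks show. If robustness is wanted, use heteroscedasticity-robust or bootstrap standard errors, pooled across the 20 imputed datasets.

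Move the rank-based comparison to a pre-specified sensitivity analysis that never replaces the primary p-value or opens the Program 2 gate. Prefer a method that keeps baseline, such as rank ANCOVA, and say how its results are combined after imputation.

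The cost is a sentence or two and a model option, with no further participants or data. Although recruitment has closed, the change can still be made before outcomes are compared by group. The one downside is that some power may be forgone if the data prove strongly skewed or heavy-tailed.
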